
### Sample Size Considerations

Based on a maximum 5-year survival probability of 20% (P=.2, *Q*=.8) and with a significance level of 5% (95% CI) and a power of 80%, it will be possible to detect a difference of 10% between 2 groups with 294 individuals per group. Table 2 shows an initial estimate of the number of survivors at 5 years available during the study period. According to preliminary data not shown, the database available for the study includes a total of 102,860 patients diagnosed with the cancers under study.

**Table 2 table2:** Incidence and estimated survival for the main pathologies under study.

Cancer	New cases each year, n	Estimated 5-year survival, n (%)	Cumulative survivors throughout the study, n
Lung	4079	738 (18.1)	3691
Metastatic colon	6128	852 (13.9)	4259
Metastatic bladder	2444	122 (5)	611
Metastatic kidney	1094	131 (12)	656
Metastatic melanoma	860	171 (19.9)	856
Pancreas	1168	96 (8.2)	479
Esophagus	616	116 (18.8)	579
Metastatic stomach	1089	57 (5.2)	283
Liver	670	118 (17.6)	590

### Ethical Considerations

Data handling will comply with Spanish Organic Law 03/2018 for data protection, the General Data Protection Regulation 2016/679, and local data protection regulations. Fundació Unio Catalana Hospitals’ ethics committee reviewed the study (CEI 18/37) and waived patient consent due to anonymized retrospective data review.

## Results

The study is currently in progress, with access to various databases. The data have undergone harmonization and curation, and they are now ready for analysis. We have initiated statistical and machine learning analyses. We anticipate discovering multiple significant associations between commonly used drugs and the survival outcomes of patients with cancer (the primary objective). Additionally, we aim to identify relevant associations between the presence of certain chronic diseases and survival outcomes in different cancer types (the secondary objective). There will be specific effects for particular cancers and general effects that impact the survival of a broad range of cancers. The initial publications containing the first relevant results are expected to be released in the first half of 2024.

## Discussion

The aim of this study is to identify drugs for commercial use for pathologies with an effect on the survival of patients with cancer. For the study, diseases that have high lethality (survival rate <20% at 5 years) will be selected because they are a priority in terms of the search for new therapies and because for these diseases, conventional treatment has had little impact on survival, which facilitates the observation of additional survival effects from other drugs. The diseases have also been selected for their high frequency, so that, despite the high lethality, the group of survivors at 5 years will be large enough to allow comparisons with the deceased group with sufficient statistical power.

Despite the good quality of the data used, this study is based on analyses of secondary data and, therefore, has certain limitations that, although hypotheses can be established, make it necessary for these hypotheses to be tested through trials that generate primary data.

First, we do not have all the variables that can act as confounding factors in patient survival. For example, we do not have data on the histology of the various tumors, which can impact survival. Especially important is also the absence of data on hospital treatment for cancer, which does not appear in any of the available databases. Due to this limitation, the study has been designed to investigate “long survivors” (5 or more years) because, for the diseases studied, there are no treatments that have been shown to extend survival to the fifth year. For this reason, it is not probable that hospital treatments act as a confounding factor (because they have no known association with the outcome studied: survival after 5 years).

Second, patient registration in the databases does not coincide exactly with disease onset, resulting in a shortened estimated time to death. This limitation is greater in the CMBD than in the ECAP databases; therefore, one database will be complemented with the other to alleviate this limitation. However, this temporal bias has an established direction: registration in the databases always occurs after the diagnosis. This allows all cases to be classified correctly in the group of patients identified as long survivors because patients who lived 5 years since their inclusion in the database will have lived at least 5 years from disease diagnosis. However, there will be a classification error whereby some long survivors, for whom their data were entered late in the databases used, will fall within the comparison group (classified as “nonlong survivors”). This error will affect at most 20% of the comparison group because that is the maximum survival at 5 years estimated for the diseases under study. Therefore, the specificity of the classification will be at least 80%, and for some cancers, it will reach 95% (such as metastatic bladder cancer or metastatic stomach cancer). This classification error will bias the results toward the null hypothesis, not invalidating the differences ultimately found between groups, although it does detract from the power of the study. Given that the magnitude of the effect sought is very large, we do not believe that the decline in power due to classification bias prevents the observation of these differences.

Third, despite the shortening of the time frame of the data analysis for each patient to control for reverse causality and “immortal patient” biases, there may be a residual effect derived from these biases within the time frame not eliminated from the analysis; however, we expect this effect to be much smaller. In addition to the aforementioned biases, there may be information biases, mainly due to pathologies not registered in the database. We do not expect that these biases will significantly affect the main variables because cancer diagnoses are usually registered in the databases used as soon as they are known, the pharmacological registry includes drugs dispensed in pharmacies (not only prescribed), and registry mortality is very reliable.

Finally, such a broad exploration of variables and results will lead to the discovery of many random results due to biological variability that may not be able to be replicated in future research. The researchers will consider the implementation of adjustments such as the “false discovery rate.” Notably, the study is exploratory, and the results must be confirmed in subsequent studies designed to test each hypothesis derived from this study.

In conclusion, this will be a pharmaco-epidemiological study with great potential to discover new drugs that influence cancer, but that, by design, will serve only as a preliminary step, guiding subsequent research aimed at the repurposing of active molecules for the treatment of cancer.

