### Participants and Settings

The study population will be patients with the following cancers whose estimated survival at 5 years is less than 20%: lung, pancreas, esophagus, gastric carcinomas, hepatocarcinoma, and metastatic cancers.

Cohort 1 will include all patients registered in the databases of the public health system in Catalonia (Spain) who were diagnosed with any of the diseases under study between 2006 and 2012 (Textbox 1 contains the list of International Classification of Diseases, Tenth Revision [ICD-10] codes) and who have complete data regarding the study variables (see “Outcome Measurements and Variables” section).

Diagnostic codes (International Classification of Diseases, Tenth Revision [ICD-10]) for the pathologies under study.

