### Outcome Variables and Measurements

The primary end point is survival, calculated from the date of entry in the database until death or until 5 years of follow-up are reached. For patients in cohort 1, the earliest date of cancer diagnosis for which they have been selected to be part of the cohort will be considered the date of entry into the study (inclusion criterion).

As study variables, the following data will be collected from all patients:

List of diagnosed diseases (data source: CMBD and ICS ECAP diagnostic registry)Date of death (data source: INE cause of death registry)Cause of death (data source: INE cause of death registry)Pharmacological treatment (data source: Catalan electronic prescription), including all prescribed active ingredients, drug withdrawal dates from pharmacies, consumed doses, and prescribed regimen, during the entire follow-up periodSex (data source: Sistema Integral d'Informació de Salut)Date of birth (data source: Sistema Integral d'Informació de Salut)Basic health area (data source: Sistema Integral d'Informació de Salut)

For the patients included in the study with one of the cancers under study (cohort 1), the following variables will also be collected:

Type of cancer and presence of metastases (data source: CMBD and ICS ECAP diagnostic registry)Date of diagnosis for which the patient is included in the cohort (data source: CMBD and ICS ECAP diagnosis registry)Surgical treatment of the cancer (data source: CMBD)Date of surgical treatment (data source: CMBD)

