### Data Curation

The data used in this study will be obtained from different databases, which must be merged for the analysis. None of the databases will be sorted by patient but by other types of entries (drugs, diagnoses, procedures performed, etc); therefore, the same patient could appear multiple times in each of them. Thus, first, a date will be associated with each event, and the information in the databases will be sorted by patient, with each patient as an entry that appears only once.

The coding of diseases and therapeutic procedures has undergone changes during the years of collection in the cohort, transitioning from using International Classification of Diseases, Ninth Revision (ICD-9) coding to ICD-10 coding. Consequently, all the data with ICD-9 coding will have to be converted to ICD-10 using the conversion tables provided by the Government of Catalonia (Generalitat de Catalunya) on their website [15].

In the pharmacological dispensing database, the active principles will be collected through the Anatomical Therapeutic Chemical (ATC) Classification System, and the amount dispensed monthly will be determined using the number of defined daily doses (DDDs) [16]. DDDs change over the years and are not uniform for different active ingredients or for drugs that form different groups as defined by the ATC4 codes. Thus, when necessary, DDDs will be transformed into units of mass for each of the drugs using the tables provided by the WHO with the evolution of DDDs over time [17].

One of the databases managed includes patients with metastases of any origin. For these patients, their previous diagnoses will be traced, and all the codes for both the CMBD and the ECAP will be analyzed to search for cancer diagnoses before metastasis to determine the origin of the cancer.

Finally, a patient rejection process will be applied based on the consistency of dates between the different databases. Following this principle, all those patients who, having been included in the database, do not have electronic prescription records will be rejected. In addition, all patients without registration or enumeration in the death databases will be excluded. Finally, patients with inconsistent dates will be excluded, for example, with postdeath records in the CMBD, ECAP, or electronic prescription.

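### The misclassification argument covers late registration only; false-positive cancer codes, which would gather among the 5-year survivors and can bias away from the null, are not considered

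*Protocol article*

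**What the plan says.** - **Entry.** Participants and Settings takes all registered patients "who were diagnosed with any of the diseases under study between 2006 and 2012" who have complete study variables. Outcome Variables and Measurements starts follow-up at "the earliest date of cancer diagnosis for which they have been selected to be part of the cohort".
- **Two sources.** The Discussion says of CMBD and ECAP that "one database will be complemented with the other to alleviate this limitation". Agreement between them is not asked for.
- **Rejection rules.** Under Data Curation, "a patient rejection process will be applied based on the consistency of dates between the different databases". Patients are dropped for having no electronic prescription record, for being absent from the death databases, or for inconsistent dates. For the metastasis database, "their previous diagnoses will be traced" to find the primary site; nothing is said about patients for whom none is found.
- **No pathology.** The Discussion states "we do not have data on the histology of the various tumors", and that hospital cancer treatment is also unavailable.
- **Misclassification.** The second limitation in the Discussion argues that registration always follows diagnosis. A patient alive 5 years after registration has therefore lived at least 5 years from diagnosis: "This allows all cases to be classified correctly in the group of patients identified as long survivors". Error is placed only in the comparison group, at no more than 20%, with the conclusion "This classification error will bias the results toward the null hypothesis, not invalidating the differences ultimately found between groups".
- **Other information bias.** The third limitation names mainly diseases missing from the records. False-positive cancer codes are not mentioned.

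**The concern.** The long survivors are the group on which the study rests, and the article discusses how someone might wrongly be left out of it but not how someone might wrongly get in. A person coded with pancreatic or metastatic cancer who does not have it (a suspicion later excluded, a benign lesion, a wrong site) has much better survival than a true patient. In a cohort where 80-95% of true patients die within 5 years, even a low rate of such codes is magnified among survivors and almost vanishes among the deceased.

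Comparing drug use in survivors and nonsurvivors is then partly a comparison of people without and with the cancer. This error does not simply dilute associations. It can create them in either direction, and because it is systematic, a larger sample makes it more significant, not less.

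**Working it through.** **Figures in the plan.** The article gives no figure for miscoding. Its sample size (20% against 30%, two-sided 5%, 80% power) reproduces at 294 per group but does not bear on this point. The Table 2 survival proportions used below also reproduce: metastatic stomach 57/1,089 = 5.2%, pancreas 96/1,168 = 8.2%, lung 738/4,079 = 18.1%.

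**Assumptions, not in the documents.** f = share of the cohort wrongly coded: 1%, 2%, 5%. q = share of those people alive at 5 years: 70-85%. Drug use in true and in wrongly coded patients, as shown below.

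**Step 1: who the survivors are.** With s the true 5-year survival:
- wrongly coded share of survivors: a = f·q / [f·q + (1−f)·s]
- wrongly coded share of nonsurvivors: b = f·(1−q) / [f·(1−q) + (1−f)·(1−s)]

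Example, metastatic stomach, f = 2%, q = 85%: a = 0.0170/(0.0170 + 0.0510) = 25%; b = 0.0030/(0.0030 + 0.9290) = 0.3%.

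Wrongly coded share of survivors, q from 70% to 85%:

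| Cancer | f = 1% | f = 2% | f = 5% |
|---|---|---|---|
| Metastatic stomach | 12-14% | 22-25% | 41-46% |
| Pancreas | 8-9% | 15-17% | 31-35% |
| Lung | 4-5% | 7-9% | 17-20% |

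The share of nonsurvivors stays below 2% throughout.

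**Step 2: odds ratio for a drug with no effect.** If true patients use it with probability p and wrongly coded people with probability r, use is a·r + (1−a)·p in survivors and b·r + (1−b)·p in nonsurvivors. Stomach, f = 2%, q = 85%, r = 40%, p = 20%: 25.0% against 20.1%, so OR = (0.250/0.750)/(0.201/0.799) = 1.33.

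Other cases, q = 85%, for f = 1% / 2% / 5%:

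| Use: wrongly coded vs true | Metastatic stomach | Lung |
|---|---|---|
| 20% vs 20% | 1.00 / 1.00 / 1.00 | 1.00 / 1.00 / 1.00 |
| 25% vs 20% | 1.04 / 1.08 / 1.15 | 1.01 / 1.03 / 1.06 |
| 30% vs 20% | 1.09 / 1.16 / 1.30 | 1.03 / 1.05 / 1.12 |
| 40% vs 20% | 1.18 / 1.33 / 1.64 | 1.05 / 1.11 / 1.25 |
| 20% vs 40% | 0.89 / 0.81 / 0.67 | 0.96 / 0.93 / 0.85 |

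Pancreas lies between: 1.12 and 1.22 for 40% vs 20% at f = 1% and 2%. The last row is a false harm.

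**Step 3: chance of P<.05.** Take N = annual Table 2 cases × 7, S = N·[f·q + (1−f)·s] survivors and the usual standard error of a log odds ratio. For stomach, N = 7,623 and S = 518, so log OR = 0.284, SE = 0.106 and z = 2.7. At f = 2% and q = 85%, the chance for stomach / pancreas is:
- 40% vs 20% use: 77% / 62%
- 30% vs 20%: 27% / 21%
- 25% vs 20%: 10% / 9%

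At f = 1% with 40% vs 20% the chance is 30% / 22%. Seven years of Table 2 cases total 18,148 × 7 = 127,036, more than the 102,860 patients held. Scaling N by 102,860/127,036 = 0.81 lowers 77% / 62% to 68% / 54%.

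**Step 4: planned safeguards.**
- *Control cohort (Statistical Analysis).* Findings also seen in controls are discarded. Controls hold no mixture of true and false cancer, so this artefact need not appear there and could be kept as cancer-specific.
- *Landmark (Methods to Address Potential Sources of Bias).* Everyone alive at 5 years was alive at the landmark, wrongly coded people included.
- *Matching and adjustment* for age, sex and diagnostic group do not identify a false code.
- *Exclusion for heightened surveillance* targets early detection of true cancers. It may remove some wrongly coded people by chance.

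**The case against.** The best defence is that the Discussion sentence answers a different question. It concerns the time origin, and for late registration the inference is sound: someone alive 5 years after registration has lived at least 5 years since diagnosis. The toward-the-null sentence likewise refers to that error. A reader might infer that the article vouches for the truth of every cancer code, or that its claim is simply false. The text supports neither; it overlooks false-positive codes and does not deny them.

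A reader might also infer a rule that a single code suffices. No such rule is written. It follows only from the absence of a confirmation step among the stated entry and rejection rules, and a fuller protocol or the planned substudy papers could contain one.

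The size is open to challenge too. The miscoding rate, the survival of wrongly coded people and the drug-use contrast are all assumed; a modest contrast brings the false-positive rate back near the nominal 5%, and the counts from Table 2 exceed the database. The surveillance exclusion and the tracing of earlier codes in metastatic patients are partial safeguards. Finally, all analyses are declared exploratory and subject to confirmation.

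All of this limits the size and severity. It leaves standing that no confirmation step is stated, that false codes would gather among survivors, and that the planned filters would not reliably remove the result. The exploratory label does not answer a systematic bias, because it affects which drugs are put forward.

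**Conclusion.** The point holds as a gap in the bias discussion and a worthwhile sensitivity analysis, not as an error that invalidates the design. If false-positive codes exist, their concentration among long survivors follows arithmetically from the choice of highly lethal cancers and is strongest where survival is lowest.

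How much this matters cannot be settled from the document. For an inert drug the distortion is nil when drug use is equal, small for lung at 1% miscoding (odds ratio at most about 1.05 in the cases shown), and substantial for metastatic stomach at 5% with a twofold contrast (1.64, or 0.67 when the contrast is reversed).

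Two stronger conclusions are tempting and unsupported: that false benefits will occur, since false harms or no effect are equally possible; and that most inert drugs would reach significance, since the 77% figure needs 2% miscoding, 85% survival, 40% against 20% use and an inflated N together.

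**What to change.** 1. In the second limitation of the Discussion, state that the correct-classification and toward-the-null statements apply to registration-timing error only. Add false-positive cancer codes as a separate bias that can run away from the null in either direction.
2. Add a sensitivity analysis restricted to patients whose cancer is confirmed on or before the landmark: a second code for the same site on another date or in the other database, or cancer surgery. Apply it equally to everyone alive at the landmark. Confirmation after that date would bring immortal time back.
3. For each highlighted drug, report whether the association holds with and without the restriction.
4. Do not rely on decedents' cause of death as the main check on code validity, because wrongly coded people are nearly absent from that group.

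As an illustration, if confirmation cut miscoding from an assumed 5% to 1% (85% alive), the wrongly coded share of metastatic stomach survivors would fall from 46% to 14%, and the inert-drug odds ratio at 40% vs 20% use from 1.64 to 1.18.

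The cost is a programming step on fields already listed for collection (dated diagnoses by source, surgery and its date). Some true patients with a single early code are lost, so precision is slightly lower in that analysis. A repeated code can also repeat an error, so the rule reduces the problem without removing it. Since the Results section says analyses have begun, the rule should be fixed before drugs are selected for publication.

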### Methods to Address Potential Sources of Bias

This study, given its retrospective nature, is potentially affected by a series of biases, whose prevention or compensation will be attempted through various techniques. The 3 most important biases are discussed below:

Reverse causality bias: drugs that are prescribed to patients near death to control their symptoms will appear associated with an increased risk of death in the analyses, with the prescription of these drugs not being the cause of death but a consequence of proximity to death. This bias will be alleviated by eliminating the drugs prescribed 3 months before death from the analysis.“Immortal patient” bias: the longer a patient survives, the more likely he or she is to be diagnosed with pathologies and to consume drugs. This can give the false appearance that the drugs consumed throughout life are the cause of prolonged survival. To control this effect, the analyses only considered the drugs consumed up to a certain date in the group of patients who survived until that same date. For example, in the group of patients who have survived at least 3 months after the diagnosis of their cancer, only drugs consumed at any time up to month 3 after the cancer diagnosis will be considered. Thus, the consumption of the drug will not be explained by longer survival because the entire group will have survived until the moment when the drugs under study are consumed. Patients who consume the study drugs after the established time cutoff point will be eliminated from the analysis. As a comparison group, only patients who have not consumed the drug at any point in their disease evolution will be taken into account.Diagnostic anticipation or “medical surveillance” bias: this bias occurs when patients are included in studies who are in a screening program for cancer because, in such programs, the cancer is diagnosed earlier, which causes the erroneous impression that the individuals live longer. In our database, patients with certain diseases may have undergone frequent diagnostic tests, thus triggering early cancer detection. For example, patients with chronic obstructive pulmonary disease (COPD) may have undergone periodic radiographs, in which lung cancer has been detected early. This may give the impression that COPD, or the drugs used by patients with COPD, are associated with increased survival from lung cancer. To control this bias, patients with a previous pathology that produces greater medical surveillance of the organ where the cancer developed will be eliminated from the analysis.

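### Late registration is said to bias only toward the null, but that holds only if the delay is unrelated to drug use; the specificity figure offered in support is mislabelled

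*Protocol article*

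**What the plan says.** The second limitation in the Discussion says that "patient registration in the databases does not coincide exactly with disease onset, resulting in a shortened estimated time to death". Of the two diagnosis sources it adds: "This limitation is greater in the CMBD than in the ECAP databases", and as a remedy "one database will be complemented with the other to alleviate this limitation". It then argues from direction: "this temporal bias has an established direction: registration in the databases always occurs after the diagnosis". Everyone classed as a long survivor is therefore classed correctly, and the only error is that some long survivors fall into the comparison group. This is put at no more than 20% of that group, from which the article concludes that "the specificity of the classification will be at least 80" percent, and up to 95% for some cancers. The argument ends: "This classification error will bias the results toward the null hypothesis, not invalidating the differences ultimately found between groups".

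The section on potential sources of bias says of medical surveillance that "patients with certain diseases may have undergone frequent diagnostic tests, thus triggering early cancer detection", and gives chronic obstructive pulmonary disease (COPD) as the example: "This may give the impression that COPD, or the drugs used by patients with COPD, are associated with increased survival from lung cancer". Patients with a condition that brings closer surveillance of the affected organ are to be removed.

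**The concern.** Knowing that registration is only ever late tells us which patients can be misclassified. It does not tell us that users and non-users of a drug are misclassified equally often, and the toward-the-null argument needs exactly that. The article gives two reasons for doubt: the delay varies by data source, and detection varies with surveillance, which is tied to the drugs a patient takes. The surveillance section accepts a timing bias away from the null; the Discussion leaves no room for one.

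The sentence carries weight because it assures readers that differences found are not invalidated. Many drugs will be screened at P=.05 without correction, so a reader may take that assurance as a reason to trust a flagged drug.

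**Working it through.** **1. The 80% and 95% figures.** Let p be true 5-year survival and s the sensitivity, meaning the share of true long survivors classed as such. The article's premise is no false long survivors.
- Specificity = true non-long survivors classed as such / all true non-long survivors = 100%, whatever s is.
- Share of the comparison group that is misclassified = p(1 − s)/(1 − ps). Its upper limit, at s = 0, is p.
- With p = 20% the limit is 20%, leaving 80%. With p = 5% (metastatic bladder, Table 2) it leaves 95%.

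This reproduces the article's figures, but as 1 − p, a lower bound on negative predictive value. Illustration with 1000 patients, p = 20% and an assumed s = 0.80: 160 long survivors are classed correctly, and 40 join 800 true non-long survivors. Specificity is 800/800 = 100%, sensitivity 160/200 = 80%, negative predictive value 800/840 = 95.2%.

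**2. When the claim holds.** Take equal sensitivity of 0.80 in users and non-users. A null drug gives 16% against 16%, odds ratio (OR) 1.00. A true 30% against 20% (OR 1.71) becomes 24% against 16%, OR = (0.24/0.76)/(0.16/0.84) = 1.66. The claim is right here.

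**3. When it fails.** Take a null drug, p = 20% in both groups, and assumed sensitivities.
- Users 0.95, non-users 0.80: 19% against 16%, OR = (0.19/0.81)/(0.16/0.84) = 1.23.
- Reversed: OR 0.81.

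In the first case 0.04/0.84 = 4.8% of the non-users classed as non-long survivors are misclassified. The 20% bound is easily met and gives no protection.

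**4. Size by delay, no landmark.** The documents give no delay, so I assume a difference d of 1 to 6 months applying to all non-users and no users. Survival is S(t) = exp[ln(S5)·(t/5)^k], with S5 from Table 2: 18.1% (lung), 8.2% (pancreas), 5% (metastatic bladder). Users are assessed at S(5), non-users at S(5 + d). With constant hazard (k = 1):

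| S5 | d = 1 month | 3 months | 6 months |
|---|---|---|---|
| 18.1% | 1.035 | 1.109 | 1.228 |
| 8.2% | 1.046 | 1.145 | 1.310 |
| 5% | 1.054 | 1.170 | 1.368 |

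Example: S5 = 5%, d = 0.5 years gives S(5.5) = 0.05^1.1 = 0.0371, and OR = (0.05/0.95)/(0.0371/0.9629) = 1.37.

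**5. Size with the 3-month landmark.** The bias section restricts analyses to patients alive at a cutoff, with 3 months as its example. Users then have S(5)/S(0.25), non-users S(5 + d)/S(0.25 + d).
- k = 1: the two are equal, so OR = 1.00 for every S5 and d above.
- k = 0.75 (falling hazard): OR 0.97 down to 0.82. The extreme is S5 = 5%, d = 6 months: 0.0686 against 0.0824.
- k = 1.25 (rising hazard): OR 1.02 up to 1.20. The extreme is the same cell: 0.0537 against 0.0453.

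The sign depends on the shape of the hazard, which is not known here.

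**6. Do the planned safeguards cover it?**
- Combining the databases and taking the earliest diagnosis date shorten the delay; the article itself claims only to alleviate it.
- The surveillance exclusion covers conditions of the affected organ, not general frequency of health care contact.
- The residual adjusters named are age, sex and diagnostic groups. Source of the entry date is not among them.
- Cohort 2 cannot detect the problem: controls have no cancer registration date, so an artefact of delay would not be reproduced there and would not be discarded.

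**The case against.** The strongest reply is that this concerns one sentence in a limitations section of a study declared exploratory throughout, that real safeguards exist, and that the landmark removes much of the effect. Much of this stands. Under constant hazard the landmark removes it completely. The no-landmark figures also count patients who die before registration as non-long survivors; for S5 = 5% and d = 6 months that is 1 − 0.05^0.1 = 26% of non-users. Delaying all non-users and no users is an extreme contrast: with 20% of users and 50% of non-users late, p = 20%, delays of 3 to 12 months and no landmark, the OR is only 1.02 to 1.15. The Discussion also says that cancer diagnoses are usually entered once known.

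A reader might infer three stronger things that the documents do not support.
- *That the delay creates false drug benefits.* The sign is not fixed; false harm is equally possible.
- *That the article itself says registration delay differs by surveillance or drug use.* It says so for data source. The surveillance passage is about earlier detection, which is relevant because the Discussion measures delay from disease onset. That primary care registration goes with drug use is inference.
- *That with so many patients such artefacts would pass P=.05.* Even for the no-landmark ORs, 80% power needs about 89,000 to 123,000 per group at 1 month and 10,000 to 14,000 at 3 months. The database holds 102,860 patients across all cancers.

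None of this rescues the sentence. A bias of unknown sign is not a bias toward the null, and exploratory status does not justify an assurance that differences found remain valid.

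**Conclusion.** The point holds in limited form. The unconditional toward-the-null statement is wrong as written: it requires delay unrelated to exposure, which the article neither states nor checks and which its own text gives reason to question. The documents do not show that the delay does differ by exposure, or by how much. Under the assumed worst case, a null drug has an OR of about 1.04 to 1.37 without a landmark and about 0.82 to 1.20 with one, so the bias is modest for short delays and unfixed in direction. The mislabelling of specificity needs no assumption; it follows from the article's own premise.

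**What to change.** - State that the error biases toward the null only if the registration delay is unrelated to drug exposure, and remove the assurance that differences found are not invalidated.
- Relabel the 80% (and 95%) as the minimum share of true non-long survivors in the comparison group, that is, negative predictive value. Say that the error lowers sensitivity.
- Record whether each patient's entry date came first from ECAP (primary care) or CMBD (hospital), and include this in the matching or adjustment.
- Report each flagged association also within ECAP-first patients, comparing effect estimates and confidence intervals. Loss of significance alone should not be read as lead time, because the subset is smaller and less precise.

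Cost: one covariate and one subset analysis, using the two sources from which the diagnosis date is already taken, plus revised wording. The downside is a less favourable statement and a less precise subset estimate. Adjusting for source will not remove delay differences that arise within one database, so the conditional wording is needed in any case.
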